**Methods:**

In this prospective multicentre cluster randomized phase-III trial patients with any incurable solid tumor and having defined cancer related symptoms, who receive new outpatient chemotherapy in palliative intention (expected tumor-size response rate ≤20%) are eligible. Immediately before the weekly visit to oncologists, all patients complete with nurse assistance the E-MO*S*AIC Assessment: Edmonton Symptom Assessment Scale, ≤3 additional symptoms, estimated nutritional intake, body weight, Karnofsky and medications for pain and cachexia. Experienced oncologists will be randomized to receive the LoMoS or not. To minimize contamination, LoMoS are removed from the medical charts after visits. Primary endpoint is the difference in global quality of life (items 29 & 30 of EORTC-QlQ-C30) between baseline and last study visit at week 6, with a 10 point between-arm difference considered to be clinically relevant. 20 clusters (=oncologists) per treatment arm with 4–8 patients each are aimed for to achieve a significance level of 5% and a power of 80% in a mixed model approach. Selected co- variables are included in the model for adjustment. Secondary endpoints include patient-perceived patient-physician communication symptom burden over time, and oncologists’ symptom management performance (predefined thresholds of symptoms compared to oncologists’ pharmacological, diagnostic or counselling actions [structured chart review]).

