## Methods

This study investigates the effect of E-MOSAIC delivered to oncologists on patient outcomes during a 6 week treatment duration applying a cluster-randomized controlled design.

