**Figure 1 F1:**
[figure not shown]
Screenshot from Palm as illustration.

The palm-based assessment consists of three elements (see screenshots in the Appendix), which are filled out by the patient (element P) and the study personnel (elements G [weight] and M [medication]).

Element P Visual-Analogue Scales (VAS) of

1. Nine frequent symptoms from ESAS (pain, fatigue, drowsiness, nausea, anxiety, depression, shortness of breath, loss of appetite, overall well-being);

For E-MOSAIC the single symptoms of the original ESAS were translated in German, French and Italian language in an informal back- and forward process, and validated preliminarily. ESAS is measured by palm in all patients.

2. Up to three optional symptoms;

3. Patients’ estimated nutritional intake.

Element G:

1. Body weight;

2. Karnofsky Performance Status;

3. Weight loss and body height (Body Mass Index calculated automatically).

Element M: pre-defined, simplified list for actual medication for:

1. Pain syndromes, including assessment of MEDD (Morphin Equivalent [oral] Daily Dose);

2. Fatigue syndromes (Methylphenidate, Erythropoietin, transfusions);

3. Anorexia/cachexia syndromes, and for edema (to control for weight changes).

After completion of the assessments the palm is put back to the docking station and the data are transferred within a few seconds from the docking station to the local computer.

The source-code of the E-MOSAIC software is copy-protected. The software is study-specific, but may be used for other purposes.

Longitudinal Monitoring Sheet LoMoS which is printed immediately and put in the patient file for the physicians’ visit by the nurse (Figure 2).

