### Data collection procedures

Patients are seen in all clinics first by oncology nurses who perform the baseline visit, educate patients about the use of the palm, ask patients about oncologist’ interventions in the previous week, and perform at weeks 3 and 6 the outcome assessments.

At baseline, weeks 3 and 6, the cognitive status of patients is assessed.

Since mild cognitive impairment is well reported to be underestimated but influencing patients’ ability to express subjective experience of well-being and symptoms, cognitive function will be monitored throughout the study (Figure 4).

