### Objectives and endpoints

The objective of the study was to evaluate the effects of the intervention using E-MO*S*AIC palm and real-time longitudinal monitoring sheet (LoMoS) in patients receiving anticancer treatment for advanced cancer in palliative intention.

Change in Global Quality of Life (G-QoL) is the primary endpoint. The difference in G-QoL between baseline and after last study visit is measured. The change in QoL will be assessed using the EORTC-QLQ-C30 composed of both multi-item scales and single item measures. Patient will complete the EORTC-QlQ-C30 at baseline and at week 3 and 6 after consultation. G-QoL is the composite score of questions 29 and 30. This instrument is well validated, frequently used and provides a large data base of normative data [32].

Secondary endpoints are the number of patients having a G-QoL response, physician-patient communication, symptoms and syndromes and symptom management performance.

Responders are defined as having a better rated G-QoL assessment after last study visit compared to baseline of more than half of standard deviation of the G-QoL changes of whole study population.

Patients’ estimation of the patient-physician communication will be assessed by a physician compassion rating and general physician attribute rating scales (27).

The rating of the physician compassion uses a semantic differential format including five pairs of physician characteristics. The characteristics are warm-cold, pleasant-unpleasant, compassionate-distant, sensitive-insensitive, caring-uncaring. The two attributes are the left and right anchor of a 100 mm line with each item ranging from 0–100. This scale has been reported to be internally consistent (Cronbach’s alpha coefficient, .92) in cancer survivors and non-cancer patients. A composite score can be calculated (ranging from 0 to 500) [33].

For general physician attributes five other pairs of statements in a semantic differential format will be used: 1) wants best for patients, 2) patient involvement in decision-making, 3) encourage patients’ questions, 4) acknowledging patients’ emotions, and 5) caring for patients. Patients will be asked to rate each of the questions in a scale of 0 (worst) to 100 (best).

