Physician’s estimation of the patient-physician communication will be assessed by a questionnaire comprising 7 ad-hoc statements covering satisfaction with amount and clarity of provided information, estimation of patients’ comprehension of information and satisfaction of patient involvement in decision making process. This evaluation tool was developed for the SAKK communication trial [34].

Symptoms and Syndromes from the E-MOSAIC software between baseline and after last study visit will be evaluated. Symptom Distress Score, the summation of the nine ESAS items is used as in the original publication [35]. All ESAS symptoms are individually investigated, to test the hypothesis, that the E-MOSAIC intervention may influence only specific symptoms (e.g., only anxiety and depression, but not pain, or vice versa). As syndromes, pre-defined selected items, the KPS, weight and weight loss, nutritional intake, and use of medical interventions for symptoms (e.g. MEDD) are compared. Several of these items have been conceptualized as clinical benefit criteria.

Number of visits with a symptom load above defined threshold for 5 symptoms without immediate intervention and all interventions performed by the oncologist to alleviate multidimensional suffering of patients and family members will be calculated and oncologists’ routine work will be collected. From the visits all routinely available information describing physician’ diagnostic or therapeutic interventions are collected: visit flow sheets, visit notes and reports, lab sheets, order sheets, and nurses’ notes.

To capture interventions made by the oncologist for any of the multidimensional (symptom) problems, which the patient recalls one week later, the patient will be asked before each visit: “did your doctor prescribe or initiated treatments or interventions to relieve your physical, emotional, or social distress/burden, and if so, please briefly mention them.”

To compare the number of interventions made for key symptoms above defined thresholds. For this study is chosen:

• visits (#) with pain > = 6/10 and no immediate change of analgesics

• visits (#) with fatigue > = 9/10 and no immediate diagnostic or therapeutic intervention

• visits (#) with anorexia > = 9/10 and no immediate diagnostic or therapeutic intervention

• visits (#) with depression > = 6/10 and no immediate diagnostic or therapeutic intervention

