• visits (#) with shortness of breath > = 6/10 and no immediate diagnostic or therapeutic intervention

A medical fellow, having at least 2 years clinical experience, who is blinded to the randomisation (the UPI system does not allow to identify institutions nor individual oncologists), will analyse for each patient the visit description and patient recalled interventions of last visit to search for such interventions.

From the visits the following variables are collected: medications and changes, diagnostic interventions, delegated interdisciplinary interventions, and patient perceived interventions.

Additional research questions investigate factors influencing change in G-QoL, tumor response (CR, PR, SD or PD), tumor type, predominant symptom, anxiety, complexity, education and hospitalization. A predominant symptom is defined as the symptom with the highest ranking and all other symptoms are > =2 / 10 lower ranked. Complexity is defined as > =3 symptoms with > =6/10, with the exception of fatigue and anorexia (threshold > =9/10).

To explore patients’ subjective adaptation to illness and burden of treatment two linear analogue self-assessment (LASA) indicators are included, assessing perceived adjustment to chronic illness (PACIS); [34] (‘no effort at all’ – ‘a great deal of effort) and overall treatment burden (‘not at all’ – ’severely’). The indicator for PACIS was confirmed to be responsive to cytotoxic side-effects, mental distress, and psychosocial dysfunction in patients with early breast cancer [36]. It is suitable to describe patients’ adaptation over time. The instruments are validated [37]. The indicator for overall treatment burden has been validated regarding side-effects of antiemetic and cytotoxic therapy [38].

As indicator for decision-making preferences, the difference in number of mismatched decision-making preferences between week 3 and 6 will be compared between the two arms.

Patients’ preferences for involvement in decision making will be assessed by a measure adapted from previous studies [39]. The patient chooses from among five categories ranging from ‘the doctor should make the decision using all that he/she knows about the treatment’ to ‘I should make the decision using all that I know and learn about the treatment’. In addition the physician is asked to choose from among the same five categories how he/she estimates the patients’ preferences.

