A mismatch is defined as follows: the patient ranks #1 or #2 and the physician #4 or #5 or vice versa. For neutral patients or physicians no mismatch is possible per definition.

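### The exploratory decision-preference mismatch indicator is a change between two on-intervention visits, so any effect already present at week 3 and sustained is subtracted out

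*Protocol article*

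**What the plan says.** In the protocol article, Objectives and endpoints, the decision-preference indicator comes after the additional research questions are introduced. Patient and physician each choose from the same five categories, the physician giving an estimate of the patient's preference. A mismatch occurs when "the patient ranks #1 or #2 and the physician #4 or #5 or vice versa". The comparison is fixed as follows: "the difference in number of mismatched decision-making preferences between week 3 and 6 will be compared between the two arms".

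The timing of intervention and assessments is given elsewhere in the article:

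- The Methods opening says that the study examines the effect "on patient outcomes during a 6 week treatment duration applying a cluster-randomized controlled design".
- The abstract's Methods paragraph says: "Immediately before the weekly visit to oncologists, all patients complete with nurse assistance" the assessment.
- Under Development of intervention tool, the resulting monitoring sheet (LoMoS) is "printed immediately and put in the patient file" for the physician's visit.
- Data collection procedures describes a separate baseline visit, after which the nurses "perform at weeks 3 and 6 the outcome assessments".

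The other change endpoints use baseline as their reference. For the primary endpoint: "The difference in G-QoL between baseline and after last study visit is measured". For the symptom endpoints: "Symptoms and Syndromes from the E-MOSAIC software between baseline and after last study visit will be evaluated".

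**The concern.** A change score isolates an intervention effect when its reference value is taken before the intervention starts. Here the reference is week 3, by which time physicians in the intervention arm have normally had the monitoring sheet at several weekly consultations. Subtracting week 3 removes whatever difference between the arms has built up by then. What remains answers a narrower question: do the arms move further apart between weeks 3 and 6?

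At stake is how this one indicator is read. If the sheet improves physicians' grasp of patients' preferences early and the improvement holds, the planned contrast understates it, in the limit to zero. If an early improvement partly wears off, the contrast points towards harm even while the intervention arm is still better at week 6.

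**Working it through.** The protocol states no rate, effect size or power for this indicator, so there is no figure to reproduce. The check is algebraic and does not depend on alpha, power or sample size.

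**Inputs from the protocol article**

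- Contrast: week 3 to week 6 difference, compared between arms (Objectives and endpoints).
- Intervention: assessment before each weekly visit over six weeks, with the sheet supplied for that visit (abstract; Methods opening; Development of intervention tool). Weeks 3 and 6 are therefore both on intervention.
- Reference time of the primary and symptom endpoints: baseline (Objectives and endpoints).

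**Notation.** I3 and I6 are the mismatch proportions in the intervention arm at weeks 3 and 6. C3 and C6 are those in the control arm.

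**Step 1. Planned contrast.** It can be regrouped as

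(I6 - I3) - (C6 - C3) = (I6 - C6) - (I3 - C3).

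It is therefore the between-arm difference at week 6 minus the between-arm difference at week 3. This regrouping does not require a stable control rate.

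**Step 2. Insert the effect.** Let the week-6 effect be I6 - C6 = -d, and let the share f be present at week 3, so that I3 - C3 = -fd. Then

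planned contrast = -d - (-fd) = -(1-f)d,

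while the direct comparison at week 6 gives -d.

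**Step 3. Numbers.** The rates are assumed, because the protocol gives none. The control rate is held constant.

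| Share f present at week 3 | Control 20%, d = 10 points: planned | Direct at week 6 | Control 30%, d = 15 points: planned | Direct at week 6 |
|---|---|---|---|---|
| 0 | -10 | -10 | -15 | -15 |
| 0.5 | -5 | -10 | -7.5 | -15 |
| 0.8 | -2 | -10 | -3 | -15 |
| 1 | 0 | -10 | 0 | -15 |

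One cell in full, for control 20%, d = 10 and f = 0.5: I3 = 20 - 5 = 15 and I6 = 20 - 10 = 10. The planned contrast is (10 - 15) - (20 - 20) = -5, and the direct one is 10 - 20 = -10.

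**Step 4. A fading effect.** Suppose the reduction is 10 points at week 3 and 5 points at week 6. The planned contrast is -5 - (-10) = +5 points, which reads as more mismatch under the intervention. The intervention arm is in fact 5 points better at week 6.

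**The case against.** **Status of the indicator.** It is neither the primary endpoint nor among the listed secondary endpoints, and no power or decision rule is attached to it. Patient-physician communication has its own instruments. This stands, and it limits the weight of the point.

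**A sustained benefit would be reported as no effect.** A reader might infer this, but the documents do not support it as a general statement. Complete cancellation needs the whole effect to be present by week 3 and then to stay flat. Growth after week 3 is captured, fully so if f = 0. The protocol gives no time course. The sheet lists symptoms, performance status, nutrition, weight and medication, with nothing on decision preferences, so any effect on this indicator would be indirect. Hence the range of f rather than a single figure.

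**Raw counts depend on how many patients answer.** A reader might also infer that comparing a number of mismatches ignores unequal response at the two visits. The Data analysis section largely meets this: it allows nonlinear mixed models or GEE for binary endpoints, and these work on patient-level data. The protocol uses the same shorthand for G-QoL response, where it also speaks of a number of patients.

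**Differencing inflates the variance.** With equal variances this holds only if the two ratings correlate below 0.5. The protocol gives no correlation, and repeated ratings by the same pair could well exceed that value. It is not evidence of a defect.

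**Physician differences.** One could defend a change score as a way to remove stable differences between physicians, which the Limitations section acknowledges may be large for communication. The protocol does not give this reason for the week-3 reference, and a week-3 reference removes a stable intervention effect along with them.

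**Looser reading.** The sentence might have been meant as mismatches observed at weeks 3 and 6. As written it describes a change, and nothing else in the article points the other way. If the looser meaning was intended, the sentence still needs rewording.

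**Conclusion.** The point holds in a limited form. The indicator is defined as a change between two visits that are both on intervention, so it estimates -(1-f)d where the arms differ by -d at week 6. For an assumed d of 10 points, the loss runs from none (f = 0) to the whole effect (f = 1), and fading after week 3 gives the wrong sign. The structure follows from the protocol's own timing. The sizes rest on assumed rates and on an unknown f.

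Nothing in the article explains why this indicator is anchored at week 3 when the primary and symptom endpoints are referenced to baseline. The consequence is confined to one additional research question. The primary and listed secondary endpoints are untouched.

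**What to change.** Reword the sentence so that the proportion of mismatched patient-physician pairs is compared between arms at week 3 and at week 6, with week 6 as the main contrast. Use the GEE or mixed model accounting for physician clusters that the Data analysis section already names, with arm, visit and their interaction. Adjust for baseline mismatch if it was collected. The text shown does not say whether it was, and the visit-schedule figure is not available here. The week 3 to week 6 change can be kept as a supplementary description of whether the arms continue to diverge.

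The cost is one sentence. The questionnaires, visits and model class stay the same.

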### Sample size calculation

Sample sizes are calculated for an inequality test for two means of change in QoL in a cluster randomized design using the software package NCSS 2004 - PASS 2002, according to the formulation of Donner and Klar, assuming a two-sided significance level of 0.05, and a statistical power of 0.8 [40]. Further assumptions on design parameters are an overall variance (s2) of 400, an intracluster correlation coefficient (ICC, estimated by the ratio of between-cluster variation to overall variance) of 0.05 , an effect size (between-arm difference in G-QoL to be detected) of 10, and the cluster size (the number of evaluable patients per physician) [40]. For the cluster size several options are considered, but it is expected to stop the trial at a cluster size of 8 with 12 physicians per arm, yielding a total sample size of 192 evaluable patients.

Since the initial estimate of the ICC might not be appropriate, an interim analysis to adjust the sample size as suggested in Lake et al. is foreseen [41]. Once data for the first 100 patients are available, estimates of within-cluster variation and between-cluster variation are obtained. If the resulting ICC has to be at least 1.5 times larger than the value taken for the initial sample size estimation, then the sample size would be adjusted using the new estimate of ICC, without alteration on other design parameters. The feasibility of patient accrual is evaluated at the same time. The recommended cluster size might be adjusted accordingly.

### Data analysis

Due to the cluster structure, comparisons of different outcomes between treatment arms will be analyzed by mixed models. For endpoints with continuous values, linear mixed model may be applied. For endpoints with categorical or binary values, nonlinear mixed model or generalized estimating equations may be applied.

The data will be stored and analyzed at the SAKK Coordinating Center using SAS software, Version 9.2 of the SAS System for Windows (SAS Institute Inc., Cary, NC, USA) and the open source R statistical software package (http://www.r-project.org/). All statistical tests will be done two-sided at a significance level of 0.05. P-values will be corrected for multiple testing where appropriate.

Descriptive statistics will be done by median and range for continuous variables. Categorical data will be reported using absolute and relative frequencies.

For the *primary endpoint*, selected influential variables (education, tumor type, predominant symptom, anxiety, complexity, hospitalisations) and the baseline G-QoL value will be included in the analysis model as covariates. For the primary analysis, only evaluable patients will be used. As a sensitivity analysis, non-evaluable patients will be included if possible. For instance, the difference between baseline and 3 weeks will be analyzed including patients who are evaluable at week 3 but non-evaluable at week 6.

Several pre-defined subgroup analyses are foreseen: The difference in G-QoL will be compared between both arms in sub-groups of patients having

a) a tumor size response (SD, PR, CR) or not (PD),

b) basic education or additional education

c) one of the main tumor types defined as composing > = 20% of the evaluable study patients.

d) a predominant symptom, if composing > = 20% of the evaluable study patients (expected based on symptom epidemiology data: pain, anorexia and/or fatigue [both predominant vs. other symptoms or alone vs. other symptoms], anxiety and/or depression [both predominant vs. other symptoms or alone vs. other symptoms], nausea, shortness of breath).

e) anxiety <6/10 or > =6/10

f) complexity less than 3 symptoms above threshold vs. > = 3 symptoms above threshold (fatigue and anorexia > =9/10, other symptoms > =6/10).

All subgroup analyses will include baseline G-QoL as covariate.

The study population will be described separately by institution (study center)-, oncologist-, and patient-related factors.

The study center will be described with regards to actual procedures of symptom and syndrome assessment at the participating institution and local available interventions for multidimensional symptom and syndrome management.

From the participating oncologists following data are collected: Gender, age, mother language, living > =6 months in the language region and Board certification oncology.

The patients included will be characterized with respect to socio-demographic variables, cognition, and disease and treatment-related variables.

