## Abstract

**Background:**

In patients with advanced, incurable cancer, anticancer treatment may be used to alleviate cancer-related symptoms, but monitoring of them in daily practice is rarely done. We aim to test the effectiveness of a real-time symptom and syndrome assessment using the E-MO*S*AIC software installed in handheld computer generating a longitudinal monitoring sheet (LoMoS) provided to the oncologists in a phase III setting.

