### Interim analysis

The interim analysis was based on the data from 89 patients coming from 31 different physicians. Of those, the data from 8 patients could not be used, since they were assigned to physicians who enrolled only one patient, i.e. they cannot be used to estimate within cluster correlation. At that time already 160 patients allocated to 47 physicians had been accrued. Unexpectedly a negative ICC was found. A literature search on negative ICCs only revealed that this appears in case of very similar but rather small clusters [42]. This translates to a negligible between-cluster variation and a dominant within-cluster variation which in turn is the case for very small ICCs. Then a simulation study using the design parameters of this trial and a SAS macro for power calculations (fpower.sas) was performed [43]. It seemed that an increasingly negative ICC does not diminish the power, but rather that the power increases further. Hence the sample size was not adapted for this reason.

However, during the interim analysis three problems arose regarding the sample size:

a) None of the predefined scenarios met the reality of cluster sizes accumulated in the first three years: instead, the vast majority of clusters were smaller than expected.

b) An unexpectedly high number of patients were not evaluable for primary endpoint according to the requirements specified in and implied by the protocol. Although the original protocol focused on evaluable patients, it did not foresee additional patients to be accrued to account for non-evaluable patients.

c) There were many clusters with only one or two or even no patients. These are problematic because they do not allow to properly calculating the within-cluster correlation required for the interim and final analysis. In fact, this renders patients who are evaluable of limited value for the analysis. While the trial design allows for varying and even small cluster sizes it is not clear how these very small clusters will affect the final results. Moreover, while there are approximate formulae to adjust the final sample size for varying cluster sizes, these only apply to approximate calculations which were not used during the trial development. These problems revealed from the interim analysis led to the following conclusions which were documented in a note to file:

1) 160 patients will be required, distributed to four patients per cluster with twenty clusters per treatment arm.

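### The primary analysis keeps only patients evaluable for the week-6 endpoint and leaves the week-3 G-QoL out of the primary model, although the accrual figures imply a large loss of patients

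*Protocol article*

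**What the plan says.** The abstract (Methods) defines the primary endpoint as the difference in G-QoL "between baseline and last study visit at week 6". Under Objectives and endpoints the assessment schedule is: "Patient will complete the EORTC-QlQ-C30 at baseline and at week 3 and 6 after consultation".

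The Data analysis section fixes the analysis set: "For the primary analysis, only evaluable patients will be used". Baseline G-QoL and several other covariates enter the primary model. The section continues: "As a sensitivity analysis, non-evaluable patients will be included if possible". As an example it says that "the difference between baseline and 3 weeks will be analyzed including patients who are evaluable at week 3 but non-evaluable at week 6".

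The Interim analysis section (under Discussion), item b), reports: "An unexpectedly high number of patients were not evaluable for primary endpoint". It then sets the target at 168 evaluable patients, says that 240 accrued patients would not have been enough because of items b) and c), and raises accrual to 264. Item c) concerns clusters with one, two or no patients. The primary analysis set is not changed.

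**The concern.** Evaluable is not defined in the article. The endpoint, and the example that separates patients evaluable at week 3 from those evaluable at week 6, imply that it turns on having the week-6 outcome. That status is settled after physicians are randomised and after patients are registered, so it can depend on how the patient fares and on which arm the physician is in.

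A complete-case change score is unbiased only if loss is unrelated to G-QoL given the covariates. The patients have symptomatic, incurable cancer and receive treatment with an expected response rate of at most 20%, so loss related to quality of life is plausible. The Strengths section names adaptation of chemotherapy through better monitoring as an aim, so the monitoring sheet could also influence who reaches week 6.

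The stated response, more accrual, restores power but repeats the same selection in a larger sample. The only sensitivity analysis described concretely compares change to week 3, which is a different endpoint. If it disagreed with the primary result, one could not tell an effect of the earlier time point from an effect of dropout.

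**Working it through.** **1. The plan's own numbers.** Inputs from the Sample size calculation section: variance 400 (SD 20), difference 10, ICC 0.05, two-sided alpha 0.05, power 0.8.
- Without clustering: n per arm = 2 x (20 x (1.960 + 0.842)/10)^2 = 62.8.
- Design effect 1 + (m - 1) x 0.05: 1.35 for clusters of 8 and 1.15 for clusters of 4.
- Noncentral t with 2(K - 1) degrees of freedom, K clusters per arm. For m = 8, K = 11 gives power 0.775 and K = 12 gives 0.813, so 12 x 8 x 2 = 192. For m = 4, K = 19 gives 0.799 and K = 20 gives 0.820, so 20 x 4 x 2 = 160.
- 160 x 1.05 = 168 and 240 x 1.10 = 264.

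The sample-size figures reproduce. The issue is the analysis set, not the required number.

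**2. Implied unusable share.** If 240 do not yield 168, the share exceeds 1 - 168/240 = 30.0%. If 264 are to yield 168, it is at most 1 - 168/264 = 36.4%, or 96 patients.

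**3. Bias if the two arms lose patients alike.** No dropout model is in the document, so these are assumptions: SD 20, correlation 0.6 between weeks 3 and 6, true effects of 7 (week 3) and 10 (week 6), and logistic dropout on the week-3 value with slope 0.04 or 0.08. Estimated week-6 difference, true value 10:

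| Setting | Slope 0.04 | Slope 0.08 |
|---|---|---|
| Completers, no clustering, unadjusted | 9.7 | 9.0 |
| Completers, 40 physicians, ICC 0.05, unadjusted | 9.6 | 8.9 |
| Likelihood model with week 3, 40 physicians | 10.0 | 9.9 |

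A simplified variant with a single dropout step gave 9.5 and 8.8 unadjusted. With baseline adjustment, at an assumed baseline correlation of 0.5 to 0.6, it gave 9.3 to 9.8. The unadjusted bias is therefore 0.3 to 1.2 points, and 0.2 to 0.7 points after baseline adjustment, all towards the null.

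**4. Bias if loss differs by arm.** Three routes, all on assumptions:
- Simple formula: bias = (p1 - p0) x D, where p is the lost share in each arm and D is how much worse the lost patients do. 0.10 x 15 = 1.5 points. The range is 0.05 x 10 = 0.5 to 0.15 x 20 = 3.0.
- Normal threshold model: the shift in an arm's completer mean is rho x 20 x phi(a)/(1 - f), where f is the lost share, a its normal quantile and phi the normal density. Lost shares of 31.0% and 41.4% give a difference between arms of 0.92 (rho = 0.3) or 1.54 (rho = 0.5). Shares of 26.4% and 46.4% give 1.78 or 2.97.
- The clustered simulation with slope 0.08 in control and 0.04 with the monitoring sheet: completers 7.3, likelihood model 9.9, so a bias of 2.7 points for completers (not baseline-adjusted).

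The effect is understated if the control arm loses more of its worse patients, and overstated if the intervention arm does.

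**5. Precision gained from week 3.** The variance ratio for the week-6 mean is 1 - r^2 x n3/(n6 + n3), with n6 = 168 and n3 the lost patients who have a week-3 value. With r = 0.4 and a quarter of the 96: 1 - 0.16 x 24/192 = 0.98, equivalent to 171 patients. With r = 0.7 and three quarters: 1 - 0.49 x 72/240 = 0.853, equivalent to 197. In the clustered simulation the standard error was about 3.4 for both methods.

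**The case against.** Several stronger readings are tempting, and the document does not support them.

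- **A third of patients deteriorate or die before week 6.** No evaluability rate, no reasons for non-evaluability and no 6-week mortality are given. The shortfall is blamed on non-evaluable patients and very small clusters together. At the interim analysis, 8 of 89 patients (9%) were unusable only because their physician had enrolled nobody else. The 264 is 240 plus a flat 10%, not derived from an observed rate. Some exclusions may be administrative. The share lost through a missing endpoint alone may thus be below 30%.
- **Week 3 is ignored, or changing the endpoint is the only remedy.** Week 3 is absent from the primary model only. The sensitivity clause is general, and the week-3 difference is one example of it.
- **The primary result will be seriously biased.** With similar dropout in both arms, the simulated bias of 0.3 to 1.2 points is small beside a standard error of 3.1 to 3.4, and smaller still with the planned baseline adjustment. The simulations also let dropout depend on the week-3 value, which favours a likelihood model using week 3 by construction. The 1 to 3 points under unequal dropout rest on an assumed imbalance.

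A fair objection also applies to the remedy. Requiring one post-baseline value still drops patients lost before week 3, and a repeated-measures model implicitly extrapolates G-QoL beyond death.

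All of this lowers the severity and shapes the fix. It does not remove the point: the evaluable-only set is a stated choice, the loss is large by the document's own account, and no firm analysis tests the assumption behind it.

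**Conclusion.** The concern holds as a should-fix improvement. The primary comparison rests on a set selected after randomisation, with an inferred 30% to 36% of accrued patients unusable; that range is an upper guide to loss through a missing endpoint. The expected bias is about 1 point or less if dropout is similar in both arms, and about 1 to 3 points against the 10-point target if it differs by arm. These sizes assume that loss is related to quality of life, which is plausible in this population but not documented. Confidence is high in the principle and moderate in mechanism and size. The case for change is protection against arm-dependent loss at low cost, using data already collected; the gain in precision is small.

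**What to change.** - **Primary analysis:** a linear mixed model for G-QoL at weeks 3 and 6 with arm-by-visit terms, baseline G-QoL and the planned covariates, a physician random effect and a within-patient covariance. Include all registered patients with a baseline value and at least one later value. The primary contrast stays the week-6 arm difference.
- **Supportive analysis:** keep the evaluable-only comparison.
- **Sensitivity analysis:** replace the conditional wording with a stated delta-adjusted analysis that penalises missing week-6 values, also covers patients with no post-baseline value, and says how deaths before week 6 are treated.

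The cost is analysis wording and some programming, with no new data and no change to the required sample size. The model relies on data being missing at random, which is weaker than the complete-case assumption but still untestable, so the delta analysis is part of the fix.
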